### Data collection

Data collection will take place from August to October 2024. This study has been approved by the Government of the Republic of Tajikistan, with the Order No. 60 and number N2148. Informed consent will be obtained from all survey respondents.

#### Sampling.

The sampling methodology for both surveys is designed to be representative of the PHC health facilities in Tajikistan at the national and oblast (region) levels. Since the role of private sector in providing PHC services is minimal in Tajikistan, the sample frame consists of all public PHC health facilities in the country comprising of- City and District Health Centers (family medicine departments), Rural Health Centers, and Health Houses. The sample was stratified across all oblasts. To obtain quality results from the comparison of the rapid phone-based HFA and the comprehensive in-person HFA, each survey will be conducted in the identical sample of 500 facilities described in Table 2.

**Table 2 pone.0309570.t002:** Sample for the rapid-phone based and comprehensive in-person HFAs.

		# Facilities	# Selected
Oblast	Dushanbe	15	15
	Sughd	616	151
	Khaktlon	1,123	150
	Gorno-Badakhshan Autonomous Region	227	84
	Districts of Republican Subordination	713	100
Type	City Health Center	41	41
	District Health Center	53	53
	Rural Health Center	895	214
	Health House	1,705	192
**TOTAL**		**2,694**	**500**
		

The enumerators will obtain verbal consent for the rapid phone-based HFA and written consent for the comprehensive in-person HFA from the respondents before starting the survey. If a respondent declines to participate, the reason for their refusal will be documented, and the facility will be replaced by a facility from the same strata whenever available. In the event of a non-response, health facilities will be replaced from a “replacement list” curated from the sample frame for each survey, following the same protocol of random sampling selection. Furthermore, in the event of a non-response, replacements for the two surveys will be done independently. This means that if a facility does not participate in the rapid phone-based HFA and needs to be replaced with another health facility, it will not be simultaneously replaced in the comprehensive in-person HFA, and vice-versa, unless the non-participation is due to the closure of the facility. As a result, the final samples may differ slightly due to varying response rates.

In both surveys, the officer-in-charge of the health facility will serve as the primary respondent. This individual is best positioned to provide comprehensive insights into the facility’s overall readiness. However, in situations where the designated officer-in-charge is unable to participate or believes another staff member would be better suited to answer specific sections or questions, the survey response could be delegated to a deputy or another qualified health worker.

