Finally, phone-based data collection is likely optimally conducted with a single respondent, given expected operational challenges with ‘passing the phone’ around the facility and/or feasibility of enumerating and then reaching multiple respondents via phone. In contrast, most large-scale, comprehensive HFAs rely on multiple respondents, often starting with the health facility manager but going on to include respondents across the health facility (e.g., service providers, pharmacist, financial administrator/accountant, etc.) in the course of a single visit. This means that the phone-based survey likely requires a careful selection of the key questions or domains that a single respondent is best suited to answer.

Despite the rise in phone-based surveys, promising early validation results, and these known limitations, there has not been a validation study of a nationally representative, phone-based HFA to our knowledge. This is a critical gap in the evidence – can phone-based surveys measure key constructs that are commonly measured via in-person HFAs? And what bias, if any, is introduced? This study will fill that gap by conducting a head-to-head comparison of a nationally representative, comprehensive, in-person HFA and a nationally representative, rapid, phone-based HFA. Our findings will have important implications on the feasibility of adopting phone-based surveys as a key complement to comprehensive HFAs to improve the timeliness and responsiveness of health systems data to better align with real-world decision-making needs.

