### Study objectives and contributions

This study has three primary objectives. The first objective is to assess the inter-method reliability of the rapid phone-based HFA compared to the comprehensive in-person HFA. This objective focuses on isolating the survey mode effect – the differences in results due to the phone and in-person administration – and will determine the extent to which phone data collection is a reliable alternative mode for conducting HFAs for a subset of key PHC service delivery indicators. To minimize bias, this objective will include only the survey questions that are identical in both the rapid phone-based HFA and the comprehensive in-person HFA. By keeping questions the same and varying only the administration mode, we can effectively isolate and examine the mode effect.

The second objective is to assess the concurrent criterion validity of indicators in the rapid phone-based HFA compared to indicators in the comprehensive in-person HFA. As discussed earlier, phone surveys require questions that are shorter, simpler, and less cognitively demanding. While this design is crucial for phone-based assessments, it can lead to issues such as questions being interpreted differently by respondents or lack of clarity or confusion on specific terms in the asked question that may affect data quality. This objective therefore focuses on evaluating the extent to which the rapid phone-based HFA can accurately measure the same underlying indicators as that in a comprehensive in-person HFA via a simplified questionnaire deemed suitable for phone-based administration.

The third objective is to compare the survey response rates and dropout rates of the rapid phone-based HFA to those of the comprehensive in-person HFA. Survey response rates are crucial for interpreting results and identifying potential biases. This is especially important for phone surveys where respondents can more easily drop out or refuse to participate in the survey. For instance, unlike for in-person surveys wherein respondents might feel more obligated to participate in a survey due to the physical presence of the interviewer, the respondents might find it easier to not answer a phone call or hang up. Additionally, phone surveys may also have higher non-response rates due to poor connectivity or time constraints faced by respondents.

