Following the mapping, a question-by-question revision activity was conducted to identify the two types of survey items mapped across both the questionnaires: (1) ‘direct’ survey items and (2) ‘indirect’ survey items. Survey items were categorized as ‘directly mapped’ when the framing and underlying indicator of the survey item were identical (or nearly identical) across both surveys. This required a one-to-one match of a question in the rapid phone-based HFA and the comprehensive in-person HFA. These survey items were commonly the ones wherein the comprehensive in-person HFA question structure was appropriate for phone administration. For instance, both surveys include the same question to identify the source of electricity at health facilities (‘What is the health facility’s main source of electricity?’). We also considered questions with identical wording across both surveys but which include enumerator verification through direct observation in the comprehensive in-person HFA “directly mapped”, because we consider in-person verification as a component of the mode effect. This includes questions on the availability and functioning of facility inputs, such as private toilets, where the enumerators in the comprehensive in-person HFA can verify the response due to being physically present in the health facilities. Directly mapped indicators will be included in objective one (reliability/mode effect) and objective two (validity) testing.

Survey items were classified as ‘indirectly mapped’ when they intended to measure similar underlying indicators in both surveys, but differed in the way they were asked or framed due to feasibility for phone administration. This typically occurred when comprehensive in-person HFA survey items were too lengthy or detailed to be administered over the phone, leading to simpler alternatives being included in the rapid phone-based HFA. For example, in measuring HIV/AIDS service provision, the rapid phone-based HFA asks whether the health facility provides HIV/AIDS services, while the comprehensive HFA asks whether the health facility was able to provide HIV/AIDS diagnosis services and HIV/AIDS treatment services in the 3 months prior to data collection. In this case, the underlying indicator “HIV/AIDS service availability” was common in both the surveys but was captured differently in each, leading to it being “indirectly mapped.”

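### Objective one says only the survey mode varies, but delegation lets different people answer the two surveys, so its agreement measures can mix mode and respondent differences

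*Protocol article*

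**What the plan says.** Study objectives and contributions gives the aim of objective one: "This objective focuses on isolating the survey mode effect". It justifies this as follows: "By keeping questions the same and varying only the administration mode, we can effectively isolate and examine the mode effect".

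The respondent rule is in the Sampling section. The default is common to both surveys: "In both surveys, the officer-in-charge of the health facility will serve as the primary respondent". The exception covers two situations: the officer-in-charge cannot take part, or "believes another staff member would be better suited to answer specific sections or questions". In either case "the survey response could be delegated to a deputy or another qualified health worker". The rule applies to each survey separately, and the article does not require the same person to answer both.

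The opening of Data analysis defines the analysis set as facilities that took part in both surveys, so the pair is a facility and not a person. Objective one: inter-reliability analysis then lists percent agreement, Cohen's kappa and PABAK, with no restriction to, or term for, the respondent. Respondent characteristics appear only under Objective two, in a regression of sensitivity and specificity.

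Indicator mapping states that in-person verification counts as a component of the mode effect. It says nothing similar about a change of respondent, and Strengths and limitations does not mention one.

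**The concern.** Two things can differ within a pair, the mode and the person answering, and the stated aim acknowledges only the first. A discordant pair in which the officer-in-charge answered one survey and a deputy the other cannot be put down to the telephone alone.

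The protocol applies a stricter standard elsewhere. It keeps indirectly mapped items out of objective one because a difference on them could have causes other than mode. A change of respondent is also a cause other than mode, and it stays in.

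What is at stake is the interpretation. The Discussion material plans to use the findings to say which domains can be collected by phone, and possibly to derive correction factors for phone data. If part of the disagreement comes from respondents, both uses would carry it forward under the name of mode.

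**Working it through.** The plan states no figure for this point, so there is none to reproduce. The check has two parts.

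**1. The sections side by side**

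| Question | What the article provides |
|---|---|
| What is claimed to vary? | Mode only (Study objectives and contributions) |
| Who answers? | Officer-in-charge by default; delegation allowed in either survey, also by section or question (Sampling) |
| What is matched? | The facility (Data analysis) |
| Does the objective one analysis account for respondent? | No term or restriction is named (Objective one) |
| What is expressly counted as part of mode? | In-person verification only (Indicator mapping) |

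The claim and the respondent rule cannot both stand as written. Randomising survey order does not settle this, because order balances what came first, not who answered.

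**2. How much it could matter (illustration only)**

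The article gives neither the share of pairs with different respondents nor the agreement between two respondents. The assumptions are:

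- item prevalence of 80%, equal in both surveys
- agreement of 0.95 when the same person answers both surveys
- agreement of 0.85 when different people answer
- a share q of pairs with different respondents

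Formulas:

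- observed agreement po = (1 − q) × 0.95 + q × 0.85
- chance agreement pe = 0.8² + 0.2² = 0.68
- kappa = (po − 0.68) / 0.32
- PABAK = 2 × po − 1

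| q | po | kappa | PABAK |
|---|---|---|---|
| 0% | 0.95 | 0.27/0.32 = 0.8438 | 0.90 |
| 10% | 0.94 | 0.26/0.32 = 0.8125 | 0.88 |
| 20% | 0.93 | 0.25/0.32 = 0.7813 | 0.86 |
| 30% | 0.92 | 0.24/0.32 = 0.7500 | 0.84 |
| 50% | 0.90 | 0.22/0.32 = 0.6875 | 0.80 |

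On the protocol's scale, strong is 0.80 to 0.90 and moderate is 0.60 to 0.79. Kappa reaches 0.80 when po = 0.68 + 0.80 × 0.32 = 0.936, that is at q = (0.95 − 0.936)/0.10 = 14%. PABAK stays in the strong band throughout.

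Variations on the inputs:

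- Different-respondent agreement of 0.80: at q = 10%, po = 0.935 and kappa = 0.255/0.32 = 0.797. At q = 50%, po = 0.875 and kappa = 0.195/0.32 = 0.609.
- Prevalence of 50% with 0.95 and 0.85: pe = 0.50, so kappa equals PABAK and goes from 0.90 at q = 0% to 0.80 at q = 50%.

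The same-respondent agreement is held at 0.95 throughout, so each fall comes from the respondent mix alone. The tables assume that different respondents agree less often; the article does not establish this.

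**The case against.** The case on the other side has real weight.

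- **The respondent is common by default.** The officer-in-charge is primary in both surveys. Data collection procedures reschedules the in-person visit when that person is absent, and provides repeated contact attempts and follow-up calls by phone. This limits delegation for unavailability. It does not limit the second trigger, where the officer-in-charge thinks someone else is better suited.
- **Exposure is limited.** Table 1 gives objective one no direct items from Services (14 questions) or Medical supplies and equipment (40 questions), together 54 of the 89. Delegation to a pharmacist or service provider would be most natural there. Some direct items are also verified by observation in person, so the in-person respondent matters less for them.
- **Respondents are not ignored.** Respondent characteristics enter the objective two regression, and direct items are part of objective two. But that model concerns sensitivity and specificity, and a characteristic such as role does not say whether the same person answered both surveys.
- **The instruments and any analysis plan are not shown.** They may already hold a same-person field, so its absence cannot be asserted. The conflict between the stated aim and the respondent rule does not depend on this.

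A reader might infer several stronger things, which the document does not support:

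- *That respondent change always makes the phone look less reliable.* A better-suited delegate could agree more closely with a verified answer. Same-person pairs are the most open to the priming described under Timing of survey administration, which could inflate agreement.
- *That respondents will differ systematically by mode.* The Introduction says "phone-based data collection is likely optimally conducted with a single respondent" and "most large-scale, comprehensive HFAs rely on multiple respondents". The second is a general remark about such assessments; the rule for this study is the same in both modes. A link with mode is plausible but inferred.
- *That facility-type comparisons are distorted.* The plan already expects large facilities to be harder for one respondent and studies that pattern.
- *That agreement labels will drop.* A scenario that starts exactly at 0.80 loses its label with any fall at all, so it shows little.
- *That admitting items "identical (or nearly identical) across both surveys" supports this point.* Set against the identical-items rule in the objectives, it is a separate, minor inconsistency of wording and unrelated to who answers.

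**Conclusion.** The point holds in a limited form. The article claims that only mode varies, yet permits the respondent to vary too, and the objective one analysis as described does not separate the two. The all-pairs results are therefore a combined mode-and-respondent difference unless respondent selection is defined as part of the mode.

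Neither size nor direction can be fixed from the document. Under the stated assumptions the loss in kappa is about 0.03 at 10% respondent change (0.8438 − 0.8125) and about 0.06 at 20% (0.8438 − 0.7813). If delegation is rare, or the same delegate answers both surveys, little changes. The planned analyses need not be abandoned, but what objective one can conclude does change, so the correction should be made.

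**What to change.** 1. In both surveys, record for each section the role of the person who answered, and whether that person also answered the other survey. If the instruments already do this, nothing needs adding.
2. Keep all facility pairs as the main objective one analysis. Add a sensitivity analysis restricted to same-respondent pairs, and report the share of pairs with different respondents. The restricted set should not become the main estimate: it selects on a fieldwork outcome and may be more affected by priming.
3. Add the same/different indicator to the regression planned under objective two.
4. Reword Study objectives and contributions so that the all-pairs result is called a combined mode-and-respondent difference. Alternatively, state in Indicator mapping that respondent selection belongs to the mode effect, as is done there for verification.

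The cost is one extra field per section, one sensitivity analysis, and a same-respondent subset that is smaller and probably weighted towards small facilities. The fourth step needs no data. It remains open if fieldwork, scheduled for August to October 2024, has ended without the field; the first three would then depend on whatever respondent information was kept.

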#### Data collection procedures.

Both surveys will involve comprehensive training for enumerators to familiarize them with survey protocols, questionnaire administration, and ethical considerations for each assessment. This will be followed by additional pilot testing the instrument in a few health facilities to identify any necessary changes and to provide enumerators with field experience before starting data collection.

At least one week before data collection commences, a data collection supervisor will contact the PHC network managers (individuals who manage several public health facilities) via phone to introduce themselves and both surveys. They will also request the names and contact information of the relevant sampled health facilities under their supervision. The PHC managers should have received the official notice from the Government regarding the surveys and that their facilities may have been included in the sample. If they do not have the official communication, the supervisor will share with them a copy of the official letter. PHC network managers will then be responsible for notifying officers-in-charge of sampled health facilities.

The rapid phone-based HFA is designed as a short 30–45 minutes survey, requiring no preparation by the officer-in-charge. Respondents will have the option to either start answering the survey during the first call, or to schedule it for a more convenient day or time. If a respondent is unreachable, the rapid-cycle survey protocol requires at least five contact attempts on different days and at varying times to complete the interview, maximizing communication success and reducing potential biases introduced by timing constraints. This will be particularly important for remote facilities with low phone connectivity, where the respondent may have sporadic access to a stable phone network. In instances where immediate completion of the interview is not feasible due to telecommunications issues or respondent availability, follow-up calls may be scheduled for a later date or time.

For the comprehensive in-person HFA, enumerator teams will contact the officers-in-charge of sampled facilities two weeks before data collection, to inform them about the survey, coordinate the date of the first visit, and share the ‘advance questionnaire’. The advance questionnaire is a subset of the comprehensive in-person HFA and comprises of questions that require reference to facility data records. This will be shared with the officer-in-charges at least two weeks prior to data collection day, allowing respondents to prepare responses, thereby saving time and improving data quality on the day of data collection.

If facilities have not received the official communication about their participation in the survey, PHC managers will be contacted to ensure that all selected facilities receive the official letter requesting their participation. For the comprehensive in-person HFA, one week before data collection, enumerator teams will again contact the officers-in-charge to confirm the date of the first visit and request completion of the advance questionnaire. This follow-up will also provide an opportunity to address any questions the officers-in-charge may have about the survey and to reschedule the first visit, if necessary. Furthermore, if on the day of data collection, the facility is closed, or the officer-in-charge is not present, or the data cannot be collected for any other reason, the enumerator teams will coordinate and reschedule the visit. If, however, the officers-in-charge refuse to participate in the study, their non-response along with their reason for refusal will be recorded, and the facility will be replaced using random sampling from the required strata.

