#### Timing of survey administration.

The comprehensive in-person HFA and the rapid phone-based HFA will be conducted as close in timing as possible, ideally within a two-week period for each health facility. The close timing of the surveys minimizes the risk of external factors (for example, a health facility receiving new medical supplies) impacting the data recorded in each survey and will ensure a more reliable comparison. However, there is a risk that conducting both surveys too close will introduce respondent fatigue that might affect results. Therefore, the order of the surveys for each health facility will be randomized to control for some of the real changes that may occur due to the order, with 50% of facilities receiving the rapid phone-based HFA first and 50% of the facilities receiving the comprehensive in-person survey first. This will allow for a more robust analysis. It will also allow us to conduct a longitudinal analysis of responses for the rapid phone-based HFA and the comprehensive in-person HFA in each facility to identify possible confounding effects depending on which survey the facility receives first. We would expect this to be a possibility especially in facilities that receive the in-person survey first, as respondent recall may be primed by the recent in-person verification of survey items and therefore, respondents may answer the rapid phone-based HFA with greater validity.

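### For mapped items that are also in the in-person advance questionnaire, phone-first facilities inside the two-week window will generally have received it before their phone call

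*Protocol article*

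**What the plan says.** Under Data collection procedures, the phone survey is described as "requiring no preparation by the officer-in-charge". For the in-person survey, "enumerator teams will contact the officers-in-charge of sampled facilities two weeks before data collection", and an advance questionnaire is shared so that answers can be prepared: "The advance questionnaire is a subset of the comprehensive in-person HFA and comprises of questions that require reference to facility data records". On its lead time: "This will be shared with the officer-in-charges at least two weeks prior to data collection day". One week before the visit the teams make contact again and ask for it to be completed.

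Timing of survey administration asks for both surveys "ideally within a two-week period for each health facility", in random order, "with 50% of facilities receiving the rapid phone-based HFA first and 50% of the facilities receiving the comprehensive in-person survey first". That section expects priming mainly where the in-person survey comes first, because recent verification may mean that "respondents may answer the rapid phone-based HFA with greater validity". The analysis section plans to compare reliability and validity by order.

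The Sampling section makes the officer-in-charge the primary respondent in both surveys, with delegation allowed. Nowhere does the article hold the advance questionnaire back from phone-first facilities until their call is done.

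**The concern.** The phone-first half is the natural place to look for phone answers given without help from the reference instrument. If the officer-in-charge already has the in-person record questions, that half is not clean for those items. The respondent may have looked up the records, or even filled in the answers, before the phone interviewer asks.

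Objective 1 sets out to isolate the mode effect, and Objective 2 judges each indicator against a 0.7 threshold. In routine use the phone survey would run every 6 to 12 months between in-person rounds, with no in-person questionnaire in circulation. Prepared answers on shared items could therefore make phone collection look better than it would be on its own. The article's discussion foresees using the results to refine the tool before scale-up in several countries, and possibly to derive correction factors, so any overstatement could carry forward.

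**Working it through.** The article gives no figure on this point to reproduce. The check is a timeline.

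**Inputs**
- Lead of the advance questionnaire before the visit: L of at least 14 days (Data collection procedures).
- Gap between the surveys: g of 1 to 14 days if the target is met (Timing of survey administration).
- Order: 50% phone first. The sample is fixed by "each survey will be conducted in the identical sample of 500 facilities described in Table 2", so 0.5 × 500 = 250 facilities are phone-first.
- Request to complete the questionnaire: 7 days before the visit.

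**Phone-first arm.** Put the visit on day 0. The questionnaire arrives on day −L and the call falls on day −g, so the questionnaire comes first whenever L > g.
- L = 14: it precedes the call for g = 1 to 13 (13 of 14 gaps) and coincides with it at g = 14.
- L = 15 or more: it precedes the call for all 14 gaps.
- The call comes first only if g > L, that is, a gap of at least 15 days, which misses the two-week target.

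**Completion request.** It falls on day −7. It precedes the call for g = 1 to 6, coincides at g = 7, and comes after the call for g = 8 to 14.

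**In-person-first arm.** The questionnaire and the visit both precede the call by design.

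**What the order comparison can see.** As a simple additive illustration for one overlapping item, let a be agreement with an unprepared respondent, e the effect of having the questionnaire, and v the effect of the visit and its verification. The phone-first arm estimates a + e and the in-person-first arm a + e + v. The difference is (a + e + v) − (a + e) = v. The contrast recovers v, but e cancels and stays inside both arms' estimates. If effects are not additive, the contrast for such an item may also be diluted.

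**Reach across items.** Table 1 gives 89 mapped items. The article does not say which are in the advance questionnaire. If, purely as an assumption, all 8 human-resources items were in it, the share would be 8/89 = 9%. The true overlap could be zero or could include every record-based item among the 89.

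**The case against.** A reader might infer that no facility at all gives an unprepared phone answer. The documents do not support that, for four reasons.

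- The questionnaire holds only record-based items. Supplies and equipment (40 items), infrastructure (15) and services (14) make up 69 of the 89, and nothing shows that they are in it. The article describes availability and functioning items as checked by observation.
- The two-week window is an ideal. Repeated call attempts and rescheduled visits are allowed, and a gap longer than the lead time puts the call first.
- Receipt is not completion. Calls made 8 to 14 days before the visit come before the completion request, and a delegate may answer the phone.
- The order comparison keeps its stated purpose. Exposure to the visit and verification still differs by randomised arm, so that effect remains estimable.

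It can also be said that needing no preparation describes respondent burden and does not promise a naive respondent, and that dispatch dates by arm belong in a field manual which an article would condense.

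The first four points stand and limit the concern to overlapping items. The last two carry less weight: the timing rules that the article does state put the questionnaire ahead of the call, no exception is given, and the priming it describes comes only from the in-person survey itself.

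**Conclusion.** The concern holds for mapped items that are also in the advance questionnaire. Among the 250 or so phone-first facilities, those meeting the two-week target will generally have received the questionnaire before the call, or on the same day at the limit of the window. For those items neither order supplies a clean unprepared phone answer. Agreement, sensitivity and specificity may be overstated relative to stand-alone phone use, and the planned order comparison cannot show it.

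The size of any bias cannot be computed, because neither the overlap with the 89 items nor the extent of preparation by the time of the call is given. The conclusion assumes that the lead time is applied alike in both arms and that at least one mapped item is in the advance questionnaire. Items outside it are not shown to be affected.

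**What to change.** **Before or during fieldwork.** In the phone-first arm, send the advance questionnaire only once the phone interview is complete. Keep the same preparation time as in the other arm, and log the send date for every facility. Preparation should not be shortened in one arm, since the reference measurement would then differ by order. The cost is a field instruction and a gap of about two weeks or slightly more in that arm: with a 14-day lead, sending on the day of the call gives a gap of exactly 14 days, and later sending lengthens it. Real change between the surveys, for example in stock, becomes somewhat more likely there.

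**In any case.** Mark the mapped items that appear in the advance questionnaire. Report Objectives 1 and 2 with and without them, and by whether the questionnaire preceded the call. If the sending rule was not changed, that last split is not randomised and may leave few facilities with the call first, so it should be read as descriptive. This costs only analysis time.

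**Headline.** Keep the pooled analysis, with phone-first results alongside. Taking the 0.7 verdicts from the phone-first arm alone would halve the sample for all 89 items and, without the change in sending, would not remove this exposure.
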